# The efficacy and safety of Fufangdanshen tablets (*Radix Salviae miltiorrhizae* formula tablets) for mild to moderate vascular dementia: a study protocol for a randomized controlled trial

**DOI:** 10.1186/s13063-016-1410-5

**Published:** 2016-06-08

**Keywords:** Vascular dementia, Randomized controlled trial, Fufangdanshen tablets, Chinese medicine

## Abstract

**Background:**

Vascular dementia (VaD) is the second most common subtype of dementia after Alzheimer's disease (AD). Currently, there are no medications approved for treating patients with VaD. Fufangdanshen (FFDS) tablets (*Radix Salviae miltiorrhizae* formula tablets) are a traditional Chinese medicine that has been reported to improve memory. However, the existing evidence for FFDS tablets in clinical practice derives from methodologically flawed studies. To further investigate the safety, tolerability, and efficacy of FFDS tables in the treatment of mild to moderate VaD, we designed and reported the methodology for a 24-week randomized, double-blind, parallel, multicenter study.

**Methods/design:**

This ongoing study is a double-blind, randomized, parallel placebo-controlled trial. A total of 240 patients with mild to moderate VaD will be enrolled. After a 2-week run-in period, the eligible patients will be randomized to receive either three FFDS or placebo tablets three times per day for 24 weeks, with a follow-up 12 weeks after the last treatment. The primary efficacy measurement will be the Alzheimer’s Disease Assessment Scale-cognitive subscale (ADAS-cog) and the Clinician Interview-Based Impression of Change (CIBIC-plus). The secondary efficacy measurements will include the Mini Mental State Examination (MMSE) and activities of daily living (ADL). Adverse events will also be reported.

**Discussion:**

This randomized trial will be the first rigorous study on the efficacy and safety of FFDS tablets for treating cognitive symptoms in patients with VaD using a rational design.

**Trial registration:**

ClinicalTrials.gov: NCT01761227. Registered on 2 January 2013.

## Background

Vascular dementia (VaD) is the second most common subtype of dementia after Alzheimer's disease (AD) [1], and it accounts for 11.1–15.8 % of all cases of dementia worldwide [2, 3]. The EURODEM Prevalence Research Group compared the prevalence of VaD in five datasets from Europe (Finland, Italy, Sweden, and two from the United Kingdom) and found that the prevalence ranged from 0.0–1.6 % for those aged between 60 and 70 years and increased to 2.8–9.2 % for subjects aged 80–90 years. The annual incidence rate was estimated to be 3.79 per 1000 among non-demented populations. At present, the treatment of VaD focuses on primary and secondary prevention strategies because randomized clinical trials in VaD have not been able to demonstrate clinically relevant symptomatic improvement. Additionally, it has not yet been possible to establish disease-modifying effects in VaD syndrome [4]. Thus, the development of an effective treatment for VaD is important.

Fufangdanshen tablets (FFDS), a traditional herbal medicine approved by the China Food and Drug Administration (CFDA) in 2008 (Number: [2008]1919), are extracted from the Chinese herbs *Salvia miltiorrhiza*, *Panax notoginseng*, and *Borneolum syntheticum* and contain tanshinone, salvianolic acid, panax notoginsenosides, ginsenoside Rb1, ginsenoside Rg1, and borneol. The tablets are used to treat patients with VaD. Preclinical studies have shown that tanshinone can improve the impaired learning and memory induced by Aβ1-40 in rat models of AD [5], inhibiting AD-induced expression levels of inducible nitric oxide synthase (iNOS) and matrix metalloproteinase II (MMP-2), reducing toxic free radicals, and suppressing oxidative injury in AD rats [6]. Salvianolic acid can inhibit glutamate release and anti-cerebral ischemic effects [7]. Borneol can improve the permeability of the blood-brain barrier [8].

Many studies have reported that FFDS tablets can improve the memory of demented mice [9] and improve the impairment of spatial discrimination and memory impairment in rat models of AD. The mechanisms may involve improvement in the brain choline acetyl transferase (ChAT) activity that is decreased in AD rats and induced by Aβ [10], lowering the toxicity of excitatory amino acids [11] and increasing the expression of vascular endothelial growth factor (VEGF) in the brains of rats during chronic cerebral ischemia [11]. Additionally, FFDS tablets could improve the learning and memory capabilities in rat models of VaD, increase the activity of superoxide dismutase, and reduce neuron apoptosis in the hippocampus [12].

A phase II clinical trial on the efficacy of FFDS tablets in VaD was carried out in five centers. The trial enrolled 231 patients; all patients were randomized to the FFDS tablets group (115 patients) or the dihydroergotoxine mesylate tablets group (116 patients). Scores on the Mini Mental State Examination (MMSE) [13] and activities of daily living significantly improved in both groups compared with baseline (*P* < 0.001). However, there were some limitations to this study. First, there was no placebo group. As all subjects knew that they were being treated with one of two drugs and all of the individuals who assessed the patients knew this as well, the results may have been influenced by a positive response bias. Second, the sample size was relatively small. Third, this previous study only followed up patients for 12 weeks, and this period of follow-up was too short to detect the effects of the drugs.

To further investigate the safety, tolerability, and efficacy of FFDS tablets in the treatment of mild to moderate VaD, we designed and report the methodology for a 24-week randomized, double-blind, parallel, multicenter clinical study.

## Methods/design

### Study design

This ongoing study was designed as a randomized, double-blind, parallel, placebo-controlled, multicenter trial (six centers). It involves a single-blind run-in (and washout) period using placebo only (2 weeks) and a double-blind treatment phase after randomization (24 weeks). The study is being carried out at six centers in China. It has been approved by the China Food and Drug Administration (code: SFDA [2008] I919) and also by the Institutional Review Board of Dongzhimen Hospital, Beijing University of Chinese Medicine and has been registered with ClinicalTrials.gov (ClinicalTrials.gov: NCT01761227). If there is any amendment to the protocol, approval must again be sought from the Ethics Committee. The patients and responsible caregivers will provide written informed consent. The study will be conducted according to Good Clinical Practice Guidelines and the principles of the Declaration of Helsinki. The protocol design is based on the guidelines of Consolidated Standards of Reporting Trials (CONSORT), and the study results will also be reported according to these guidelines.

### Participants

This trial will enroll both outpatient and inpatient Chinese-speaking males and females aged 45–80 years old, weighing 45–90 kilograms, and meeting the diagnostic criteria of probable VaD established according to the Diagnostic and Statistical Manual of Mental Disorders, 4th edition (DSM-IV) [14], the National Institute of Neurological Disorders and Stroke, and the Association Internationale pour la Recherche et l’Enseignement en Neurosciences (NINDS-AIREN) [15].

Participants’ inclusion criteria are described as follows:Dementia Global cognitive impairment and defects in at least one other cognitive domain such as executive function/attention, information processing speed, visual spatial ability, language and memory, which can be confirmed by clinical and neuropsychological assessment, and Cognitive impairment severe enough to interfere daily living and functioningCerebral vascular diseases, such as clear neuroimaging (MRI or CT) evidence of ischemic stroke, including infarct in the main blood vessels, single strategic infarct (e.g., thalamus, angular gyrus, and basal forebrain), multiple lacunar infarcts, and/or extensive white matter damage surrounding ventricles (≥25 % of all white matter area). Focal neurological signs that can be explained by stroke are also necessary, such as hemiplegia, anesthesia, hemianopia, dysarthria, facial paralysis, and positive reflex of Babinski’s signCorrelation between dementia and cerebral vascular diseasesThe dementia occurs within 3 months following a stroke, orEvidence of sudden onset, stepwise progression, focal cortical deficits on neuropsychological assessment, andHachinski Ischemic Scale (HIS) score >4 [16] and 6-month VaD duration before inclusionSeverity of dementia assessed as mild to moderate as defined by a score of 11 to 26 on the MMSE [13]Patients must have adequate vision and hearing to participate in study assessments

Patients who confirm any of the following excluding criteria conditions will not be enrolled in the study: subjects with AD and any other secondary types of dementia (e.g., post-traumatic dementia, dementia associated with Parkinson’s disease, or cerebral tumor); depressive pseudodementia and other mental disorders; a history of epilepsy; patients suffering from psychotic episodes; psychomotor excitation; MRI scans not showing vascular lesions in the brain; a history of drug or alcohol abuse in the past 6 months; acute or uncontrolled chronic illnesses; history of hypersensitivity to the treatment drugs; concomitant drugs with the potential to interfere with the study outcomes (including anticonvulsant agents, psychotropic drugs, drugs with psychiatric side effects, anticoagulants, cholinomimetic agents, short-acting benzodiazepines, or any other drugs that contain *Salvia miltiorrhiza*, *Panax notoginseng*, and/or *Borneolum syntheticum*); participation in another clinical study.

All subjects will undergo an MRI scan before they are randomized. Participants will be excluded if the MRI presents medial temporal lobe atrophy adjusted for age. Scans will be performed routinely at each site and will be considered adequate if the images are of sufficient technical quality to be read accurately for the purposes of determining study inclusion. After receiving this imaging information, investigators will consider the clinical history, examination, and laboratory evaluations to assign the designation of “probable VaD” or “possible VaD.”

### Study medication

All trial medication will be supplied by the Hutchison Whampoa Guangzhou Baiyunshan Chinese Medicine Company Limited (China). The FFDS tablets are composed of *Salvia miltiorrhiza* (DanShen in Chinese), *Panax pseudo*-*ginseng* (SanQi in Chinese), and *Borneolum syntheticum* (BingPian in Chinese). Each tablet weighs 0.3 g and contains tanshinone, salvianolic acid, panax notoginsenosides, ginsenoside Rb1, ginsenoside Rg1, and borneol. The FFDS tables were produced in a single batch (batch number: 080401, Placebo batch number: 081101) in strict compliance with standards of Good Manufacturing Practice (GMP).

During the 2-week placebo washout period, all patients will receive three placebo tablets three times per day. During the double-blind, 24-week intervention, the patients will receive either three FFDS or placebo tablets (three times per day), at least 2 hours apart from taking any routine Western medication. To preserve blinding, the placebo tablets have an identical taste and appearance to the FFDS tablets.

Concomitant use of anticonvulsants, antipsychotics, cholinomimetic drugs, anticholinergic agents, anti-Parkinson drugs, cholinesterase inhibitors, memantine, nootropic drugs, nimodipine, other cognition enhancers, or any drugs containing *Salvia miltiorrhiza* and *Panax notoginseng* will be forbidden. The investigator must record the concomitant drugs, including the name of the drug, daily dose, reason for using, and date of termination.

### Sample size calculations

Because there are few studies on the treatment of VaD, the sample size was calculated based on data from a study of AD treatment using the Alzheimer’s Disease Assessment Scale-cognitive subscale (ADAS-cog) [17]. The previous study reported that patients who received donepezil (5 mg/day) showed a mean improvement of 0.67 ± 0.51; the patients who received the placebo showed a worse score of 1.82 points. Using a one-sided test with a significance level of 0.05 and power of 90 %, the minimum number was 88 per group to detect a difference of 1.5 points on the ADAS-cog. To achieve an adequate number to detect the safety of the FFDS tablets, the number of the patients was increased to 100 per group. Considering a greater rate of discontinuation of 20 %, the sample size was increased to 120 per group to ensure adequate patients to complete the study.

The randomization is stratified according to center using SAS statistical software (version 9.13) (SAS Institute Inc., Cary, NC, USA). Balanced randomization generated by SAS statistical software is carried out in three steps (in blocks of four) by a statistician with no access to information on the patients or physicians. Patients will be randomized in a ratio of 1:1 to receive the FFDS or placebo tablets. The randomized code is generated in the randomization process and sealed in an envelope. Statisticians assign the medication group according to the randomization code. Afterwards, the sealed randomization codes and each available medication number are sent out to each center. Blinding will be broken only if a patient’s trial medication requires specific emergency treatment. Once the blinding is broken, the patient will be managed as off-trial.

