### Statistical analysis

Statistical analyses will be conducted in three populations. The intent-to-treat (ITT) population will consist of all of the randomized population who take at least one dose of medication and at least one primary efficacy evaluation on treatment. The fully evaluated (FE) population will include all randomized patients who have received at least 80 % of the assigned 24 weeks of double-blind medication with a complete record of efficacy variables, with no major protocol violations. The safety set (SS) population will include all of the randomized population who receive at least one dose of the study medication, with at least one safety record post baseline.

The efficacy analysis will be conducted with the ITT and FE populations. The ADAS-cog and CIBIC-plus will be analyzed using the last observation carried forward (LOCF) method for the replacement of missing observations. The ADAS-cog and MMSE will be assessed by analysis of covariance (ANCOVA) with baseline scores as covariates and the treatment group and center as factors. The Cochran–Mantel–Haenszel test will be used for CIBIC-plus scores. The occurrence of adverse events will be analyzed using frequency calculations and descriptive statistics.

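### The trial is sized on an unexplained one-sided 5 % test against placebo, the only significance level stated; it should be two-sided 0.05, with power restated

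*Protocol article*

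**What the plan says.** The level and direction of the test appear once, under Sample size calculations in the protocol article: "Using a one-sided test with a significance level of 0.05 and power of" 90 %. From this the article concludes that "the minimum number was 88 per group to detect a difference of 1.5 points on the ADAS-cog". For safety, "the number of the patients was increased to 100 per group", and an allowance for 20 % discontinuation brings the total to 120 per group, allocated 1:1 to FFDS or placebo.

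The only dispersion figure is in the summary of the Alzheimer's disease study used for planning, whose donepezil patients "showed a mean improvement of 0.67 ± 0.51". The article does not say whether 0.51 is an SD, a standard error or something else.

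The Statistical analysis section assigns ANCOVA to the ADAS-cog and says that the Cochran–Mantel–Haenszel (CMH) "test will be used for CIBIC-plus scores". It gives no significance level and no direction for either primary endpoint.

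**The concern.** The trial sets out to show superiority over placebo. The usual standard for that is a two-sided 5 % test, which leaves 2.5 % for a false finding of benefit. A one-sided 5 % test leaves 5 %. Such a choice needs a reason, and the article gives none, although its abstract calls the existing evidence methodologically flawed and presents this trial as the first rigorous one.

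Two things are at stake. First, if the one-sided level is the success criterion for the ADAS-cog, a difference favouring FFDS with a two-sided p-value between 0.05 and 0.10 would pass while its 95 % confidence interval still included zero. Second, if the final test is two-sided, the sample size statement describes a test that will not be performed, and its 90 % is too favourable for 88 per group. One of these applies, and either calls for a correction.

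**Working it through.** **Inputs, all from Sample size calculations.** Difference 1.5 ADAS-cog points; one-sided level 0.05; power 90 %; 88 per group; 1:1 allocation; raised to 100 and then 120 per group; 20 % discontinuation, so 120 × 0.80 = 96 completers per group. No SD is stated.

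**Step 1: reproduce 88 per group.** For two means, n per group = 2 × SD² × (z_α + z_β)² / δ², with z_α = 1.645 (one-sided 0.05) and z_β = 1.282.

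- Taking 0.51 as the SD: 2 × 0.51² × 2.926² / 1.5² = 1.98, so 2 per group. This does not reproduce 88.
- Solving for the SD that gives 88: SD = 1.5 × √(88/2) / 2.926 = 3.40. With the t distribution in place of the normal it is 3.39.

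So 88 is consistent with a one-sided calculation at an SD near 3.4. That SD is an inference, used below as an assumption.

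**Step 2: error rate.** Under no effect, a one-sided 0.05 test declares benefit with probability 0.05. A two-sided 0.05 test does so in the benefit direction with probability 0.025. For a single endpoint the ratio is 2.

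**Step 3: effect on sample size.** At 90 % power, moving to two-sided 0.05 multiplies n by ((1.960 + 1.282) / (1.645 + 1.282))² = 1.227, whatever the SD or difference. Hence 88 × 1.227 = 108 per group.

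**Step 4: effect on power.** With the normal approximation, power = Φ(δ / (SD × √(2/n)) − z_α). At SD 3.40:

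| n per group | δ / (SD × √(2/n)) | One-sided 0.05 | Two-sided 0.05 |
|---|---|---|---|
| 88 (stated minimum) | 2.926 | 90.0 % | 83.3 % |
| 96 (120 less 20 %) | 3.057 | 92.1 % | 86.4 % |
| 100 | 3.120 | 93.0 % | 87.7 % |
| 120 (randomized) | 3.417 | 96.2 % | 92.7 % |

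The noncentral t at SD 3.39 gives the same values to within about 0.1 point (two-sided: 83.2, 86.3, 87.6 and 92.7 %), and 108 per group gives 89.97 %.

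**Step 5: what could pass.** At 96 per group and SD 3.40 the standard error is 3.40 × √(2/96) = 0.491. One-sided 0.05 requires an observed difference of 1.645 × 0.491 = 0.81 points; two-sided 0.05 requires 1.960 × 0.491 = 0.96. Differences from 0.81 to 0.96 would pass only the first.

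**Step 6: other SDs**, since 3.4 is an assumption:

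| SD | n for 90 %, one-sided / two-sided | Power at 96, one-sided / two-sided | Power at 120, one-sided / two-sided |
|---|---|---|---|
| 3 | 69 / 85 | 96.6 / 93.4 % | 98.7 / 97.2 % |
| 4 | 122 / 150 | 83.0 / 73.8 % | 89.6 / 82.8 % |
| 5 | 191 / 234 | 66.8 / 54.7 % | 75.1 / 64.2 % |
| 6 | 275 / 337 | 53.5 / 41.0 % | 61.5 / 49.1 % |

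**The case against.** The one-sided level appears only in the sample size paragraph. The analysis section is silent, and the final test may be fixed in a statistical analysis plan that is not shown. This stands, and it makes the 5 % false-benefit rate conditional. It does not remove the point: a two-sided final test would leave the published power computed for another test.

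The power loss is also modest for the trial as planned. The 83 % belongs to 88 per group, which is not the final size. The intent-to-treat set requires one dose and one on-treatment primary evaluation, with the last observation carried forward, so many patients who discontinue still count. At the back-solved SD, two-sided power stays near or above 90 % unless more than about 12 per group (120 − 108) have no such evaluation. This stands too.

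Three stronger readings are tempting and not supported:

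- A reader might infer that the primary endpoints face different false-benefit rates, 5 % for ADAS-cog and 2.5 % for CIBIC-plus, because the CMH statistic is a chi-square without direction. The usual ANCOVA F test has no direction either, and with two groups a CMH mean-score test can be signed. The article gives neither level nor direction for either analysis, so no such mismatch is in the text.
- A reader might infer that the chance of the whole trial falsely declaring benefit is doubled. The article does not state whether both primary endpoints must succeed or either suffices, so the doubling can be claimed only for ADAS-cog tested on its own.
- A reader might infer that the one-sided choice leaves the trial underpowered. At the back-solved SD, 120 per group still give about 93 % two-sided. At larger SDs power falls below 90 %, but from SD 4 upward it does so one-sided as well (89.6 % at 120 for SD 4), so sidedness is not the main cause there.

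**Conclusion.** The point holds, with limits. The article sizes a placebo-controlled superiority trial on a one-sided 0.05 test, without justification, and states no other level. If that level governs the ADAS-cog analysis, the false-benefit rate on that endpoint is 5 % where 2.5 % is conventional. If it does not, the 90 % at 88 per group does not describe the test to be used.

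On a two-sided 0.05 test, power is about 83 % at 88, 86 % at 96 and 93 % at 120 per group, and about 108 evaluable per group give 90 %. These figures rest on an SD of about 3.39 back-solved from 88. The 22.7 % increase in required n and the factor of 2 in the single-endpoint error rate do not depend on it. The correction is worth making, but the recruitment target need not change on this account.

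**What to change.** Before unblinding, state that ADAS-cog (ANCOVA) and CIBIC-plus (CMH) will each be tested at two-sided 0.05, equivalently one-sided 0.025, and that treatment effects will be reported with 95 % confidence intervals. Restate the power on that basis, giving the SD used and its source. If 3.39 is that SD, the statement would read about 86 % with 96 evaluable per group and about 93 % with 120.

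The timing is favourable: the article reports the trial as ongoing with 212 subjects, and blinding is kept until all data are collected. Made after unblinding, the same change would look data-driven.

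The change is to wording, with no added patients or visits. The cost is a less favourable power figure: at SD 3.39, about 7 points lower at 88 per group, 6 at 96 and 3 at 120. At a larger SD the drop is greater, for example 9 points at 96 per group for SD 4 (83.0 to 73.8 %).

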### Procedures

Two methods are being used to recruit participants with VaD. The first source of subjects is from memory clinics of six public hospitals of different centers, and the second source is those who respond to advertisements published in local newspapers. Figure 1 shows the schedule of enrollment.

**Fig. 1 Fig1:**
[figure not shown]
Schedule of enrollment. *ITT* intent to treat

The neuropsychological assessments, laboratory determinations, measurements of vital signs (including temperature, blood pressure, and electrocardiogram), and neurological tests (including an examination of cranial nerves, motor coordination, muscle tonus, and power) will be evaluated before patients are enrolled. The diagnosis of probable VaD will be based on the neurological test and confirmed by the criteria of the NIND-AIREN and DSM-IV, the HIS, and the Hamilton Depression Rating Scale (HAMD) [18]. For differential diagnosis, the Activities of Daily Living (ADL) [19] and a scan of the brain are also necessary.

All patients will receive an assessment at baseline (0 week), 12 weeks, and 24 weeks, and an additional assessment will be performed 12 weeks after completing the assigned double-blind medication. The study timeline and endpoints are shown in Table 1.

**Table 1 Tab1:** Study timeline and endpoints

Items	−2 weeks (run-in)	0 week (baseline)	12 weeks (mid-term follow-up)	24 weeks (endpoint)	36 weeks (follow-up)
Inclusion criteria		√			
Exclusion criteria		√			
MRI scan	√				
Informed consent	√				
General information	√				
Vital signs	√	√	√	√	√
MMSE	√	√	√	√	√
HAMD	√				
HIS	√				
ADAS-cog		√	√	√	√
CIBIS		√			
CIBIC-plus			√	√	√
ADL		√	√	√	√
Safety measure		√	√	√	
Adverse event		√	√	√	
Concomitant drugs		√	√	√	√

*CIBIS* Clinician Interview-Based Impression of Severity, *CIBIC-plus* Clinician Interview-Based Impression of Change

Any adverse events will be recorded during the duration of the trial. Patients will receive four clinical assessments.

Patients, caregivers, the study investigator, any other personnel involved in the study, and the investigating staff of the Hutchison Whampoa Guangzhou Baiyunshan Chinese Medicine Company Limited will remain blinded until all patients complete the study and all data are collected.

